## Abstract

**Background:** Transcatheter aortic valve implantation (TAVI) has become the standard-of-care for treatment of severe symptomatic aortic stenosis and is also being increasingly recommended for low-risk patients. While TAVI boasts positive post-procedural outcomes, it is also associated with cognitive complications, namely delirium and cognitive decline. There is a pressing need for accurate risk tools which can identify TAVI patients at risk of delirium and cognitive decline, as risk scores designed for general cardiovascular surgery fall short. The present effect-finding exploratory study will assess the utility of various measures in the context of aging and frailty in predicting who will and who will not develop delirium or cognitive impairment following TAVI. The measures we propose include gait, visual symptoms, voice, swallowing, mood and sleep.

**Methods:** This is an observational prospective cohort study focused on identifying pre-procedural risk factors for the development of delirium and cognitive decline following TAVI. Potential risk factors will be measured prior to TAVI. Primary outcomes will be post-procedure cognitive decline and delirium. Secondary outcomes include activities of daily living, quality of life, and mortality. Delirium presence will be measured on each of the first 2 days following TAVI. All other outcomes will be assessed at 3-, 6-, and 12-months post-operatively. A series of logistic regressions will be run to investigate the relationship between potential predictors and outcomes (presence vs. absence of either delirium or cognitive decline).

**Discussion:** This study will assess the strengths of associations between a range of measures drawn from frailty and aging literature in terms of association with cognitive decline and delirium following TAVI. Identified measures can be used in future development of TAVI risk prediction models, which are essential for the accurate identification of cognitive at-risk patients and successful application of pre-procedural interventions.

**Clinical Trial Registration:** This trial is registered with the Australian New Zealand Clinical Trials Registry. [https://bit.ly/2PAotP5], [ACTRN12618001114235].

## Introduction

Severe symptomatic aortic stenosis is a heart condition which affects one-in-ten people over the age of 75 (1). Surgical aortic valve replacement was traditionally the usual treatment for this condition, yet approximately one third of patients are unsuitable for surgery due to older age or comorbidities (2). In 2002, transcatheter aortic valve implantation (TAVI) was introduced as a non-surgical alternative for the treatment of severe symptomatic aortic stenosis and has since become the standard of care in the large number of patients with prohibitive surgical risk (3). Recommendation for TAVI treatment has been extended to low-risk patients in recent years (4, 5). During a TAVI procedure, a new valve is positioned into the heart from a blood vessel in the groin or an anterograde transapical approach, thus circumnavigating the need for cardiopulmonary bypass and sternotomy (6).

While TAVI is associated with positive post-procedural outcomes, such as lower mortality and improvements in quality of life (7–9), cognitive complications including delirium and cognitive decline are common (10, 11). Delirium is an acute and fluctuating disorder of deficits in attention and arousal (12). A previous meta-analysis by our group found that one-in-four TAVI patients experience delirium in the days following their procedure (10). In older individuals delirium is associated with a range of poor outcomes including functional decline, loss of independence, cognitive decline and dementia, institutionalization and death (13, 14). Furthermore, another meta-analysis by our group demonstrated that cognitive decline is seen in up to 14% of patients in the year following TAVI (11). Cognitive decline can lead to clinically significant cognitive impairments including mild cognitive impairment (MCI) and dementia (15, 16).

Given the frequency of these poor cognitive outcomes, there is a pressing need for tools and methods which accurately identify those at increased risk of developing delirium and cognitive decline following TAVI. Identification of those at risk allows for the implementation of pre-procedural education, multicomponent intervention and appropriate community follow-up in these patients (17). The current study is an effect-finding study, which looks to examine the utility of several potential factors related to incident delirium and cognitive decline. These include those that were identified by our meta-analysis (10), are currently used in delirium risk tools for general cardiac patients (18, 19), and novel factors previously unexplored in this context, identified from the broader aging and frailty literature. Notably, previous tools (18, 19) have focused on delirium not cognitive decline. These factors related to delirium within previous tools and our meta-analysis are outlined in Table 1.

**Table 1 T1:** Risk factors from existing prediction models for post-cardiac procedure delirium and from meta-analysis of post-TAVI delirium predictors.

**Variable**	**Katznelson et al. (18)** ^*****^	**Rudolph et al. (19)** ^*****^	**Tilley et al. (10)** ^***†***^
**Pre-procedural variables**			
Abnormal albumin		✓	
Age	✓		
Atrial fibrillation			✓
Cognitive impairment		✓	✓
Coronary artery disease			✓
Depression	✓	✓	
EuroSCORE			
Hypertension			✓
Peripheral vascular disease			✓
Renal dysfunction	✓		✓
Statin use (protective)	✓		
Stroke history		✓	✓
**Intra-procedural variables**			
Valve access type			✓

* *Prediction model for cardiac procedures*.

† *Meta-analysis for TAVI*.

To our knowledge, there are no risk prediction models for post-procedural cognitive decline in TAVI patients or cardiac patients generally. A recent meta-analysis (11) reported that the use of cerebral embolic protection devices and pre-procedure cognitive impairment reduced the risk of post-TAVI cognitive decline. Within the context of an aging population, there is a general rising demand for pre-operative risk stratification of older adults to aid informed consent and the guiding of patient expectations (20). Risk scores such as European System for Cardiac Operative Risk Evaluation (EuroSCORE) and Society of Thoracic Surgery (STS) are currently widely used as part of pre-TAVI evaluation. However, these scores were developed for conventional cardiovascular surgery and are limited in their predictive utility for TAVI patient populations (21–25).

In the absence of specific risk tools for TAVI, measures of frailty have been recommended (26–28) and have demonstrated reasonable success in predicting adverse post-operative outcomes (29, 30). Frailty is a problematic expression of aging which represents increased vulnerability to sudden health changes in response to only minor stressor events (31). This clinical condition, affecting between 25 and 50% of those over 85 years old, develops as a result of accelerated age-related decline across multiple physiological systems (31). A growing body of evidence over recent years has demonstrated that frailty and other functional measures are predictive of worse outcomes, such as mortality, after TAVI (28, 32–39). Specific to delirium, a meta-analysis has demonstrated a significant association between frailty and delirium, with frail individuals carrying a 2-fold increased risk of subsequent delirium (40). In TAVI patient populations, there have been conflicting accounts on the relationship between frailty and post-operative delirium (41–43). This lack of consensus may be due to differences in the frailty measures employed, and lack of clarity regarding which features of frailty carry the most predictive utility in a TAVI sample. Research has demonstrated that frailty increases risk of incident Alzheimer's disease and cognitive decline (44). Only one study (45) has investigated differences in pre-procedural frailty between those who did and did not develop cognitive decline following TAVI, with no difference found. However, once again, only one frailty measure was used, and individual components of frailty were not investigated.

The concept of frailty emerged from epidemiological studies and measures have generally been composed of relatively blunt items (e.g., the presence or absence of a health issue) (31). At a population-based level, these frailty measures have shown to predict mortality and morbidity well (39). In smaller clinical samples, there is great opportunity to develop more sensitive measures that capture frailty and aging processes. We propose to assess the utility of various measures in the context of aging and frailty in predicting who will and who will not develop delirium or cognitive decline post-TAVI. It is not our purpose to develop a new measure of frailty *per se*, but rather employ knowledge of aging and frailty processes to inform our selection of new risk measures of delirium and cognitive decline in TAVI patients. The measures we propose include gait, visual symptoms, voice, swallowing, mood and sleep. All of these have previously been associated with aging, dementia, cognitive decline, or neurodegeneration, and are easy to collect in clinical settings.

High dual-task gait cost (the change from single-task to dual-task gait speed) associates with a 2- to 3-fold increase in incident dementia risk in those with existing MCI (46). In TAVI populations, impaired mobility has also been related to post-operative delirium and reduced quality of life (33, 47). Research has shown eye blink rate to be significantly higher or lower in those with cognitive impairments. A higher blink rate has been found in MCI (48), while a lower blink rate has been reported in those with Parkinson's disease, as compared to controls (49). Visual symptoms could also have utility, particularly convergence, which can lead to diplopia (double vision) and is seen in neurodegeneration (50). Dysphagia (difficulty swallowing) has also been found in a wide variety of neurodegenerative disorders associated with aging, including Parkinson's disease (51). Finally, depression has been identified as a large predictor for delirium following cardiac procedures (52) and is included in existing prediction models (18, 19). We will include not only depression, but also more broad measures of neuropsychiatric symptoms including insomnia (53). In order to maximize potential clinical applicability, the novel symptoms we are introducing and investigating within the context of post-TAVI delirium and cognitive decline are easily implemented in clinical settings with minimal training and equipment.

In summary, this study will investigate associations between a wide range of factors and post-TAVI delirium and cognitive decline. Existing risk scores (STS and EuroSCORE), factors incorporated within current delirium risk prediction tools, and factors with reported associations to post-operative delirium will be evaluated. In addition to this, we will include a range of novel measures which are drawn from the literature of aging and frailty. The aim of this effect-finding study is to identify potential measures from which to develop risk prediction models for cognitive decline (at 3-, 6-, and 12-months post-procedure) and delirium specifically for TAVI patients. Such risk prediction models will aid in the identification of at-risk patients, allowing for earlier and targeted intervention to reduce the occurrence of delirium and cognitive decline following these procedures.

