#### Potential Risk Factors

All potential factors to be measured are presented in Table 2, along with their duration and the time-points of the study at which they are assessed.

**Table 2 T2:** Measures and assessments utilized throughout study period, with approximate collection time.

**Assessments**	**Duration (min)**	**Baseline**	**D1**	**D2**	**3 M**	**6 M**	**12 M**

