#### Sample Characteristic Data

##### Population Characteristics

General population characteristics will also be collected in order to characterize the sample. These measures include age, gender, years in education (including primary, secondary and any further formal education), height, waist circumference, weight, and body mass index. Level of social engagement and physical activity will be collected by self-reported rating of the frequency participants see a member of their family or friend and take part in physical activity. Response options for these self-reports are daily, weekly, fortnightly, monthly, less than monthly, and never.

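### Abnormal albumin and statin use, two of the seven factors from the existing delirium tools, are missing from the list of what is measured, so the stated evaluation of tool factors is incomplete

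*Protocol article*

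**What the plan says.** The Introduction commits twice to covering the factors in existing tools. Where it describes the study's candidate factors, it includes those used by the two published delirium tools for cardiac patients (references 18 and 19), and adds: "These factors related to delirium within previous tools and our meta-analysis are outlined in Table 1". Its closing summary then says that "factors incorporated within current delirium risk prediction tools, and factors with reported associations to post-operative delirium will be evaluated". Neither statement names an exception.

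Table 1 gives the factors by source. "Abnormal albumin" is ticked once, for the tool in reference 19. Statin use, labelled as protective, is ticked once, for the tool in reference 18.

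The Potential Risk Factors section opens: "All potential factors to be measured are presented in Table 2". The Medical History and Procedural Factors section says what is taken from hospital records, and refers back to Table 2 for the items. Data Analysis then enters each predictor into a separate model for each outcome, with no multivariable models and no correction for multiple comparisons.

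**The concern.** The product of this study is a list of variables to carry into larger samples for building TAVI-specific risk tools. A factor that is never recorded can be neither put forward nor set aside. If the text promises the factors of the existing tools but the data collection leaves some out, a reader of the results could take their absence to mean that they were tested and found unhelpful. The gap would also fall on factors with a claim to attention, since each already sits in a published cardiac delirium tool.

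An article may leave detail to a fuller document, and silence alone would be no finding. Here the article is not silent. It states that Table 2 holds all the potential factors, and that statement does not fit the commitment in the Introduction.

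**Working it through.** No figure in the plan is at issue, so the check is a row-by-row comparison of Table 1 with Table 2.

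**Step 1. Factors ticked for the two tools in Table 1.**

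- Reference 18: age, depression, renal dysfunction, statin use (4).
- Reference 19: abnormal albumin, cognitive impairment, depression, stroke history (4).
- Depression is in both, so the distinct factors number 4 + 4 − 1 = 7.

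**Step 2. Counterparts in Table 2.**

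| Tool factor (Table 1) | Tool | Row in Table 2 |
|---|---|---|
| Age | ref. 18 | Age |
| Depression | both | Geriatric Depression Scale |
| Renal dysfunction | ref. 18 | Renal disease |
| Statin use | ref. 18 | none |
| Abnormal albumin | ref. 19 | none |
| Cognitive impairment | ref. 19 | ACE-III at baseline |
| Stroke history | ref. 19 | Previous stroke/TIA |

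Five of seven have a counterpart and two do not (2/7, about 29%). Each tool keeps three of its four factors.

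**Step 3. Could the two factors be collected elsewhere?**

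- Table 2 has no row for a blood test and none for medication.
- The record extraction is defined by reference to Table 2, so it adds nothing further.
- The only medication item described is in the Frailty section: an Edmonton Frail Scale question on whether five or more prescription medicines are taken regularly. It does not identify a statin.
- EuroSCORE II and the STS score appear as whole scores. The article does not list their components, so they cannot be read as supplying either factor separately.

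**Step 4. Is the gap wider?** Table 1 has 13 rows (12 pre-procedural, 1 intra-procedural). All eight factors ticked for the TAVI meta-analysis have a Table 2 row: atrial fibrillation, cognitive impairment, coronary artery disease, hypertension, peripheral vascular disease, renal dysfunction, stroke history and valve access type. The EuroSCORE row carries no tick but is also matched. Albumin and statin use are therefore the only unmatched rows (13 − 11 = 2).

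**The case against.** The strongest reply is that the commitment is not explicitly exhaustive. The Introduction does not say that every tool factor will be evaluated, it speaks of several potential factors, and the record extraction is described as pertinent history. Neither missing factor is ticked for the TAVI meta-analysis, so leaving them out could have been deliberate. The study is exploratory, and Table 1 keeps both candidates in view for later developers. Part of this stands: it limits the consequence. It does not remove the mismatch, because the unqualified wording, with its pointer to Table 1, naturally means the listed set, and no reason for an omission is given.

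Three stronger readings are tempting, and the article does not support them.

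- *Embolic protection is also missing.* A reader might infer this because the Introduction reports that "the use of cerebral embolic protection devices and pre-procedure cognitive impairment reduced the risk of post-TAVI cognitive decline" and Table 2 lists only access type and procedure time as procedural factors. But that finding concerns cognitive decline, embolic protection is not a row in Table 1, and the commitment quoted above is about delirium factors. The study is also framed around pre-procedural risk factors. Its absence contradicts nothing.
- *Age is not treated as a predictor.* The Population Characteristics section says: "General population characteristics will also be collected in order to characterize the sample". Age is nevertheless in Table 2, the same table that is said to hold the potential factors. Its labelling is ambiguous; it is not absent.
- *A comparison of novel with established factors is compromised.* None is planned. The article speaks of evaluating factors, and Data Analysis specifies single-predictor models only.

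**Conclusion.** The point holds in a limited form. Two of the seven distinct factors that Table 1 attributes to the existing cardiac delirium tools are not among the factors to be measured, so the evaluation announced in the Introduction cannot be completed as written.

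The effect on the rest of the study is small. Because each predictor is modelled alone, the omission biases no estimate for a measured factor and changes no outcome or sample-size input. What is lost is any evidence on albumin and statin use in this cohort. The point is still worth correcting, because the inconsistency touches a stated objective and the remedy is cheap.

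The conclusion assumes that the rows and ticks of Tables 1 and 2 are complete as they appear in the article, and that the statement about Table 2 covering all potential factors is meant literally. If albumin and statin use are in fact being collected, the error lies in Table 2 and only the table needs correcting.

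**What to change.** Add pre-procedural albumin and statin use to Table 2 as items extracted from hospital records, and run the same univariate models for them as for the other predictors. For participants already enrolled, extract both retrospectively, and record any value not in the record as missing. If the records cannot supply one or both, narrow the two statements in the Introduction to the tool factors actually measured and give the reason. One further sentence could confirm that age is analysed as a predictor.

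The cost is a few more fields in a record review that the Procedure section already schedules for each participant, plus two univariate models per outcome. For the primary outcomes (delirium, and cognitive decline at three follow-ups) that is 2 × (1 + 3) = 8 more uncorrected tests. If each is judged at the 0.05 level used in the Sample Size section, about 8 × 0.05 = 0.4 false positives would be expected among them were there no true associations. This is consistent with the plan's stated exploratory approach. How often albumin was measured before the procedure cannot be judged from the article, so the amount of missing data is unknown. The models for other factors are unaffected.

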##### Medical History and Procedural Factors

Pertinent medical history, risk scores and procedural factors (see Table 2), based on those identified through previous research, will be collected from Royal Adelaide Hospital records.

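### Two of the seven factors in the existing cardiac delirium tools, abnormal albumin and statin use, are to be evaluated but are not among the factors collected

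*Protocol article*

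**What the plan says.** The Introduction describes three groups of factors to be examined: those from the authors' own meta-analysis, those that "are currently used in delirium risk tools for general cardiac patients (18, 19"), and novel measures from the ageing and frailty literature. It then directs the reader to a list: "These factors related to delirium within previous tools and our meta-analysis are outlined in Table 1". The last paragraph of the Introduction repeats the commitment: "factors incorporated within current delirium risk prediction tools, and factors with reported associations to post-operative delirium will be evaluated".

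Table 1 has one column for each of the two prediction models (references 18 and 19) and one for the meta-analysis. The row "Abnormal albumin" is ticked only for the reference 19 model. The statin row, marked as protective, is ticked only for the reference 18 model.

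The Potential Risk Factors section then fixes what is collected: "All potential factors to be measured are presented in Table 2". The section on Medical History and Procedural Factors refers to the same table and says that its items "will be collected from Royal Adelaide Hospital records". The Procedure section also points to Table 2 for the record review done before TAVI.

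**The concern.** The Introduction commits the study to evaluating a set of factors and shows the set. The Methods give a variable list, described as complete, that lacks two of them. A factor that is not collected cannot enter any of the single-predictor regressions in the Data Analysis section.

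This matters because of what the study is meant to produce. Its stated purpose is to propose variables to carry into larger, independent samples for building TAVI-specific risk tools. A reader who takes the Introduction at its word would see albumin and statin use missing from the proposed variables and conclude that they had been examined and had shown nothing. Statin use is also the only factor that Table 1 marks as protective.

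**Working it through.** **The article's one design calculation.** The Sample Size section gives n = 44 for r = 0.4, power 0.8 and α = 0.05. With a two-sided point-biserial test, the noncentrality is √n · r/√(1 − r²) = √44 × 0.4/√0.84 ≈ 2.90 on 42 degrees of freedom. The power is 0.807, and 44 is the smallest n that reaches 0.8. The figure reproduces. It does not depend on how many predictors are collected, so nothing below changes it.

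**Factors in the two tools (Table 1).**
- Reference 18 model: age, depression, renal dysfunction, statin use (4).
- Reference 19 model: abnormal albumin, cognitive impairment, depression, stroke history (4).
- Depression is in both, so the distinct factors number 4 + 4 − 1 = 7.

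**Match against Table 2.**

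| Tool factor (Table 1) | Model | Entry in Table 2 |
|---|---|---|
| Age | 18 | Age |
| Depression | 18, 19 | Geriatric Depression Scale |
| Renal dysfunction | 18 | Renal disease |
| Cognitive impairment | 19 | ACE-III at baseline |
| Stroke history | 19 | Previous stroke/TIA |
| Statin use | 18 | none |
| Abnormal albumin | 19 | none |

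Five of seven are collected. Two of seven (2/7 = 29%) are not, one from each model.

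**Could either item come in by another route?** Table 2's items from hospital records are six medical history conditions, two surgical risk scores and two procedural factors. None is a laboratory value or a drug. The only medication question in the article is the Edmonton Frail Scale example asking about five or more regular prescriptions. That is a count and does not identify a statin.

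**Is the table simply damaged in the text?** The meta-analysis column of Table 1 has eight factors: atrial fibrillation, cognitive impairment, coronary artery disease, hypertension, peripheral vascular disease, renal dysfunction, stroke history and valve access type. All eight have a Table 2 entry, and Table 2 runs on to items such as waist circumference and social engagement. The gap is confined to the two tool factors, and the article gives no reason for leaving them out.

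**The case against.** The strongest reply is that the commitment is looser than it sounds. Neither statement in the Introduction says that all the tools' factors will be evaluated. The article speaks of several potential factors, and the section on medical history describes a pertinent selection drawn from earlier research. The study's emphasis is on gait, vision, voice, swallowing, mood and sleep, and none of those analyses changes. Table 1 keeps albumin and statin use in view for anyone who later builds a model. On this reading, one narrowing sentence removes the problem.

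Part of this stands. Narrower wording would remove the contradiction, and no analysis of a collected factor is affected. But the closing statement of the Introduction carries no qualifier, Table 1 is offered as the list, and nothing tells the reader that two of its entries were set aside. Article condensation does not explain the gap, because the article itself calls Table 2 complete.

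A reader might infer two stronger things, and the article supports neither.

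- *That the study fails because neither delirium tool can be scored in this cohort.* Scoring those tools is never promised. The existing scores named for evaluation are STS and EuroSCORE, and both are in Table 2. Table 1 gives ticks only, without weights, cut-offs or definitions, so the article does not show that a total could be formed even with both items added.
- *That eight planned primary tests are lost* (2 factors × [delirium + decline at 3, 6 and 12 months] = 2 × 4 = 8). The Data Analysis section plans regressions only for factors measured in the study. Tests of these two were therefore never planned. The Introduction also notes that the earlier tools addressed delirium rather than cognitive decline.

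**Conclusion.** The concern holds as an inconsistency between the stated aim and the stated data collection. Two of the seven distinct factors in the existing cardiac delirium tools cannot be tested under the plan as written, so that part of the aim cannot be delivered. Their absence from the proposed variables would reflect non-collection and not lack of association. It should be corrected, but it is modest in scale: the planned regressions for all collected factors and the sample size stand.

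The conclusion assumes that Table 2 is the complete list it is said to be, and that the Table 2 entries matched above are fair counterparts of the Table 1 factors. Age is counted as collected because it is in Table 2. The article also lists it among the sample characteristics, and whether it will be entered as a predictor is a separate question that does not alter the count of two. Whether albumin and statin use can be recovered from the hospital records is not stated.

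**What to change.** Add two rows to Table 2 and two fields to the hospital-record extraction described under Medical History and Procedural Factors and under Procedure: the last serum albumin before TAVI, and statin use before TAVI. Extract both retrospectively for participants already enrolled. Enter each as a single predictor in the models of the Data Analysis section, and report how many values are missing for each. If albumin is analysed as abnormal versus normal, state the cut-off before the analysis, since Table 1 gives none.

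If either item cannot be obtained from the records, change both statements in the Introduction to say that a selection of the tools' factors is evaluated, and name those not collected. No tool total score is proposed.

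The cost is two chart items for at most 60 participants whose records are already reviewed, and possibly a minor ethics notification. No extra patient contact or change in sample size is needed. The main drawback is that albumin may be missing for some patients.
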